### Intervention

The RESPOND intervention involves catalysing systems change through community-led collective action. It comprises four main components adapted to be delivered at-scale from the process described by Sweeney et al. [34]. RESPOND aims to engage whole communities in a locally led multifaceted response. Implementing the four components of the intervention is intended to disrupt the current trajectory of obesity prevalence by instigating actions around the modifying determinants of childhood obesity (e.g. physical activity, sedentary behaviour, poor diet quality and sleep insufficiency). In brief, the four components include the following (Table 2):

**Table 2 Tab2:** Four components of the RESPOND intervention

Component	Description
Component 1: Catalyse and Set up	Establishment of strong governance within partnership group with clearly defined roles and responsibilities of the partners. Identification of capacity for component 2.
Component 2: Monitoring	Routine childhood obesity and risk factor surveillance/monitoring system. Data will be collected every 2 years.
Component 3: Community engagement	Local leaders receive relevant training in group model building and facilitation.
Component 4: Implementation and diffusion	Implementation of community-led actions and networking opportunities between communities.

The intervention comprises four components: Within the first component (Catalyse and set up), strong governance will be established within the partnership group, and the roles and responsibilities of different partners will be established. Routine meetings of the partnership governance group will be established to maintain engagement and prioritisation of the intervention. To catalyse and prepare for the commencement of the intervention at each step, key partners in each region will identify capacity to support the monitoring and community engagement components described below.

The second component (Monitoring) will be a routine childhood obesity and risk factor surveillance/monitoring system to be established across the 10 LGAs, with data collection repeated every 2 years. Data collection is supported by locally based prevention capacity identified in component one. In addition to supporting overall evaluation of RESPOND, key statistics on children’s weight status and health behaviours will be provided to support the community engagement component—providing impetus for community action and context around the current state of child health in the communities.

In the third component (Community engagement), local leaders receive training in group model building (GMB) and facilitation techniques. Recruitment to these training sessions were snowballed from local leaders (identified in the first component). Attendance is regularly encouraged to maximise adherence to the prescribed GMB process during delivery. Following training, facilitators will recruit local leaders and champions into group model building workshops to develop a causal loop diagram (CLD) of the communities perceived drivers of childhood obesity, as they apply to their community and context. Following the development of the CLD, facilitators will support community leaders and champions to design intervention actions to be implemented and led by the community.

Within component four (Implementation and diffusion), community-led actions are implemented. Community stakeholders will share with the researchers the ‘actions’ identified within their group model building workshops. Alongside implementation, active communities will be connected with each other and with the research team via monthly meetings as an ‘implementation network’. This network will form a forum for communities to share learnings on effective strategies to support and guide community actions as they emerge. The research group will assist the stakeholders to identify effective strategies to support local actions, but will not directly participate in the operational management of actions. Reminders will be sent at least 1 week prior to the event for all training and workshop activities and attendance registers will be kept.

The explanation above outlines the intervention, and more detail is available in the trial registration [31]. The exploration of the change in knowledge and engagement over time, as outlined in this protocol, is one key element of this study. The intervention has been funded through an Australian National Health and Medical Research Council (NHMRC) Partnership Project grant (1151572), in partnership with 12 organisations; partners have committed > $3.5 m—a mix of staff time and cash contributions. Ethics approval has been obtained from Deakin University Faculty of Health Human Ethics Advisory Group (HEAG-H 173_2018) and for the childhood obesity monitoring system by Deakin University’s Human Research Ethics Committee (2018-381), the Victorian Department of Education and Training (2019-003943) and the Catholic Archdiocese of Melbourne and Sandhurst. All invited participants will provide informed consent prior to gaining access to the online survey. There will be no special criteria for discontinuing or modifying allocated interventions.

### Outcomes

The SDCD will measure levels of knowledge and engagement prior to commencement, during intervention (annually, 2019–2023) and at the end of the intervention (2023). The Regional Partners Group and Implementation Network will be surveyed at all five time points, while the community-specific Community Action Groups will be surveyed annually from the time the groups come into existence post GMB 3 (2019 for step 1, 2021 for step 2).

#### Primary outcomes

Baseline overall knowledge and engagement scores across the three levels of governance: Regional Partners Group, Regional Implementation Network and Community Action Groups.Change in overall knowledge and engagement since baseline across the three levels of governance.

#### Secondary outcomes

Changes in knowledge and engagement sub-scales over time since baseline across the three levels of governance between 2019 and 2023.Association between baseline and/or changes in knowledge and engagement with the type and level of community-led actions matched against the variables and connections identified in the causal loop diagrams created. For example, active travel as a variable may result in specific actions such as the construction of bike storage or bus drop-off zones to improve active travel.

### Recruitment

The survey will be completed online, and all potential participants will receive an email link to the survey. The Regional Partner Group will be directly invited to participate by the researchers, through contact lists for the RESPOND project quarterly meetings, which are convened and chaired by the University-based operational team (Fig. 2). The project partner organisations are responsible for convening the RIN and CAG; therefore, through third party recruitment, these partner organisations will send the survey invitations to all participants at those levels so that the researchers and partner agencies do not break the Victorian Privacy and Data Protection Act 2014 [35]. Based on previous experience of our group in similar surveys, we anticipate a response rate of 65% for the RPG and RIN and a response rate of 40% for the CAG.

### Data collection

Data will be collected using a modified version of the Stakeholder-driven Community Diffusion Survey (SDCD) developed by Korn et al. [28]. This survey developed by Korn et al.’s [28] was informed by extensive work with communities implementing interventions using a stakeholder-driven community diffusion model [12] and an in-depth review of the core elements of capacity building that are specific to community-based participatory childhood obesity prevention interventions [11]. This work identified strong community engagement as being associated with positive intervention outcomes, and the development of effective coalitions in turn built community capacity, particularly in the fields of leadership [28]. This tool is designed to be simple to administer and capture the elements of community capacity that are directly relevant to the community and systems-based approach and childhood obesity focus of the RESPOND intervention.

Our modified survey consists of 43 questions across five knowledge domains and five engagement domains (see Additional file 1). The networks components of the SDCD survey will be omitted. The data will be collected via the online survey platform Qualtrics [36] and takes 10–15 min to complete. Respondents are asked to answer knowledge and engagement questions on a five-point scale: strongly disagree, disagree, neutral, agree, strongly agree. High levels of knowledge are characterised by an understanding of obesity prevention at the community scale, encompassing knowledge of the problem, intervention factors, stakeholder roles, sustainability and resources. A person with little understanding of these factors would likely have no or low levels of relevant knowledge, which would be expected to impede diffusion of an evidence-informed intervention through a community. High levels of engagement represent positive characteristics on the five domains of dialogue and mutual learning (for example, openness and collaborative behaviours), flexibility, influence and power, leadership and trust (for example, high levels of trust in colleagues and commitment to promoting a climate of trust and collaboration). Across the 10 domains, the survey aims to efficiently capture all relevant domains of community capacity that are hypothesised to influence intervention outcomes and/or be impacted by intervention implementation. Limited personal data will be collected, such as age and years of experience in the field, and a unique identifier will be assigned during analysis to enable tracking of responses over time.

The survey was minimally modified for the RESPOND intervention to ensure appropriateness to the local context and intervention. Our intervention specifically relates to children aged under 12 years, so the phrase ‘age range 0 to 12 years’ was added. Two further questions related to resources were added, based on a recent systematic review of sustainability of community-based obesity prevention interventions where ‘resources’, both human and financial, were identified as the most cited reason for sustainability of interventions [37]. These two questions were pilot tested with the RESPOND Regional Partner Group in December 2018 and wording was edited until the group agreed that the meaning was clear. This amended SDCD is available in Additional file 1 (additional items are questions 16 and 17 in Domain 5: Available resources). More detail is shown in Table 3.

**Table 3 Tab3:** Knowledge and engagement survey structure

Survey structure	No. of questions
**Section 1 Knowledge**	
Domain 1: The problem of childhood obesity	5
Domain 2: Modifiable determinants of childhood obesity (intervention factors)	3
Domain 3: Sustainability	3
Domain 4: Stakeholders’ roles	3
Domain 5: Resources	5
**Section 2: Engagement**	
Domain 1: Dialogue and mutual learning	7
Domain 2: Flexibility	3
Domain 3: Influence and power	2
Domain 4: Leadership and stewardship	10
Domain 5: Trust	2
**TOTAL**	**43**

### Data management and analysis plan

The responses to each SDCD survey question will be coded from 0 (strongly disagree) to 1 (strongly agree) [0 = 0 strongly disagree, 0.25 = disagree, 0.50 = agree, 0.75 = agree, 1.00 = strongly agree]. Domain summaries are the average of items within each domain. Participant summaries are averages of the domains (domain-weighted rather than item-weighted). We view the domains as equally important as each other, and the number of items is not related to how important the domains are, rather the complexity of eliciting the information about each domain. The SDCD survey will be summarised at participant level as the average of items within each of the five domains of knowledge (5 knowledge sub-scores) and the five domains of engagement (5 engagement sub-scores) (see Table 3).
*Analysis*: RQ1: What is the baseline level of community leaders’ knowledge and engagement in each of the governance and implementation groups within the project and how does it differ between communities?

Variability of scores and sub-scores of knowledge and engagement at baseline across participant communities will be estimated based on surveys completed by participants in the Local Implementation Groups. Of note, ‘baseline’ corresponds to the 2019 survey for step 1 communities and to the 2021 survey for step 2 communities. Variability across communities will be estimated using a linear mixed model (multi-level) with community as the random factor.
*Analysis*: RQ2: How do levels of knowledge and engagement among community leaders change during participation in a whole-of-community systems intervention?

We will fit linear mixed models with time as fixed effect and participant as random effect (to account for the repeated measurements) to assess whether a temporal trend exists in the SDCD scores (and sub-scores) and whether the intervention induces changes in trends of SDCD scores. For Regional Implementation Network participants/communities, the model will further include community allocation to step 1 or 2 as fixed effect, and the breakpoint (2021) to allow for changes in slope in step 2 communities. For Local Implementation Groups, the model will additionally include community as a random effect to account for clustering. If for any participant group a linear relation between a given score and time is not supported by the data, time will be incorporated as a categorical variable.
*Analysis*: RQ3: Explore whether average community baseline knowledge and engagement levels and/or average community changes in knowledge and engagement levels are associated with implementation effectiveness of system-level intervention.

For each community, data on knowledge and engagement of community leaders at baseline and changes in knowledge and engagement will be summarised using location and dispersion measures. We will explore whether these measures are associated with implementation effectiveness (number of actions implemented by the community) using nonparametric correlation and if appropriate linear models.

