#### Problem statement

Despite increasingly complex intervention approaches, there has been little progress in understanding how community leaders’ knowledge, engagement and social networks contribute to the success or otherwise of community-based interventions. This is partly due to a historical focus on evaluating outcomes from single community trials, with less emphasis on the specific characteristics that may lead to successful outcomes within these trials and across broader multi-community trials.

This paper presents the protocol for the measurement and evaluation of knowledge and engagement among community leaders’ for the Reflexive Evidence and Systems interventions to Prevent Obesity and Non-communicable Disease (RESPOND) trial, a whole-of-community systems intervention across 10 large intervention communities (local government areas (LGAs)) in Victoria, Australia. This protocol follows the SPIRIT checklist for guidance in the reporting of protocols for clinical trials [29]. The measurement of leaders’ knowledge and engagement over multiple time points, along with intervention process measures, will enable investigation of the following research questions:
RQ1: What is the baseline level of community leaders’ knowledge and engagement in each of the governance and implementation groups within the project and how does it differ between communities?RQ2: How do levels of knowledge and engagement among community leaders change during participation in a whole-of-community systems intervention?RQ3: To explore whether knowledge and engagement levels, and/or changes in knowledge and engagement levels, predict implementation effectiveness of system-level intervention?

Our hypothesis is that there will be heterogeneity between intervention sites on baseline levels of knowledge and engagement and that these differences will be associated with variability in implementation success and level of intervention within a system. The level of system intervention actions will be evaluated against the Meadows framework [30]. This assessment includes, for example, changes to a variable, connections between these variables, rules governing the system and goals of the system [30].

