## Methods

RESPOND utilises systems approaches in the design, implementation and evaluation of a large-scale intervention to prevent obesity among children aged 0–12 years. It has prospective registration as a clinical trial [31], and is a stepped-wedge cluster randomised trial in 10 communities. This protocol explains one sub-study of the RESPOND trial that relates to changes in knowledge and engagement.

The setting for the trial is the Ovens Murray and Goulburn regions of north eastern Victoria, Australia Fig. 1, which covers a population of approximately 30,000 children (aged 0–12 years) [32]. For the purpose of trial design, communities are defined as local government areas (LGAs), which are the geographical divisions administered by municipal governments within Australian states and the Northern Territory [33]. The unit of randomisation and intervention (clusters) is the LGA (rather than individual children or townships). The ten LGAs will be ranked in order of population size and divided in five pairs. A computer-generated random list will be generated by the study statistician who will not be involved with any aspect of the enrolment process and has no contact with the communities. One community from each pair will be randomly allocated to receive the intervention at step 1. Blinding is not feasible in this trial as the whole community is recruited into the design, implementation and evaluation.

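### RQ2 asks of every tier whether the intervention changes score trends, but only the Regional Implementation Network has surveys that can separate exposed from unexposed time

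*Protocol article*

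**What the plan says.** The research question is descriptive: "How do levels of knowledge and engagement among community leaders change during participation in a whole-of-community systems intervention". The analysis paragraph for RQ2 goes further. It gives the linear mixed models a double purpose, "to assess whether a temporal trend exists in the SDCD scores (and sub-scores) and whether the intervention induces changes in trends of SDCD scores", and does so before any tier is mentioned, so on its face it covers all three.

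The tiers then differ:

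- **Network.** The model gains step allocation as a fixed effect and a breakpoint at 2021 for step 2 communities.
- **Action groups** (called Local Implementation Groups here). "For Local Implementation Groups, the model will additionally include community as a random effect to account for clustering". No step term is named.
- **Partners group.** No further term is given.

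The survey calendar is in Outcomes. "The Regional Partners Group and Implementation Network will be surveyed at all five time points", whereas the action groups are "surveyed annually from the time the groups come into existence post GMB 3 (2019 for step 1, 2021 for step 2"). Allocation is paired and random (Methods): "One community from each pair will be randomly allocated to receive the intervention at step 1".

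**The concern.** To say that an intervention changed a trend, one needs observations not yet exposed to it: a prior slope, a concurrent unexposed comparator, or both. If a tier has neither, its time coefficient is the sum of any intervention effect and whatever else moved scores in the region over 2019 to 2023, and no model can divide the two. Change in overall knowledge and engagement since baseline is a primary outcome. A reader of the results could therefore take an uncontrolled calendar slope as the answer to the causal half of the stated aim.

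The action groups do carry some randomised information, because both steps are surveyed in 2021, 2022 and 2023. The plan does not clearly say that this will be used, or what it would measure.

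**Working it through.** **1. The plan's own count.** Inputs are from Table 1 and the text below it: 44 partners-group members, 10 network members, 10 action groups of up to 100, five waves in step 1 and three in step 2. With five communities per step:

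- partners group 44 × 5 = 220
- network 10 × 5 = 50
- step 1 action groups 5 × 100 × 5 = 2500
- step 2 action groups 5 × 100 × 3 = 1500
- total 4270, as stated.

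Five waves for everyone would give 1054 × 5 = 5270. The stated maximum therefore confirms that step 2 action groups contribute nothing before 2021.

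**2. Unexposed waves by tier.**

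- *Action groups: none in either step.* Group model building is part of the intervention (component 3), Table 1 defines members as workshop participants, and the first survey follows GMB 3.
- *Partners group: at most one, 2019.* The Abstract speaks of measurement before commencement, Table 1 proposes Feb/Mar 2019, and Trial status dates step 1 recruitment from April 2019. Against this, component 1 acts on the partnership group itself and is undated, so the wave's status is unclear.
- *Network, step 2: two (2019, 2020),* or three if the 2021 survey precedes the start.

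**3. What each calendar can estimate.** This is the rank of the fixed-effect design over step-by-year cells, with t = year − 2019.

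| Tier | Terms | Rank / columns |
|---|---|---|
| Action groups | categorical year + exposed (yes/no) | 5 / 6 |
| Action groups | categorical year + step | 6 / 6 |
| Action groups | categorical year + step + years since formation | 6 / 7 |
| Action groups | intercept, t, step, step × t, step 2 breakpoint at 2021 | 4 / 5 |
| Partners group | intercept, t, slope change at 2019 | 2 / 3 |
| Network | categorical year + exposed (yes/no) | 6 / 6 |
| Network | intercept, t, step, step × t, step 2 breakpoint at 2021 | 5 / 5 |

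In the first row, every action-group cell is exposed, so the indicator equals the sum of the year columns. In the fourth, step 2 has no cell before 2021, so the breakpoint term equals step × t − 2 × step. Without step × t the model has rank 4 of 4, but the breakpoint then measures only how the step 2 slope differs from step 1, not a change within step 2.

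The action-group step contrast is estimable in 2021 to 2023. It compares about 2, 3 and 4 years since formation with about 0, 1 and 2.

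**4. Size.** The partners and action groups hold 220 + 4000 = 4220 of 4270 observations (98.8%). If the 44 partners-group observations of 2019 are counted as unexposed, 4176 remain (97.8%). Step 2 network members before 2021 give at most 5 × 2 = 10 observations, or 6.5 at the anticipated 65% response.

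**5. Illustration; drift, SD and ICC are assumptions.** A regional drift of d per year adds 4d to step 1 scores between 2019 and 2023: 0.08 at d = 0.02, with 0.04 and 0.16 at half and double that. For the 2021 action-group contrast, take 40 respondents per community (100 × 40%) and SD 0.15, with SE = √[(2/5) × 0.15² × (ICC + (1 − ICC)/40)]:

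| ICC | SE | 95% half-width, 8 df (t = 2.306) | 95% half-width, 4 df, paired (t = 2.776) |
|---|---|---|---|
| 0.02 | 0.020 | 0.046 | 0.056 |
| 0.05 | 0.026 | 0.059 | 0.072 |
| 0.10 | 0.033 | 0.077 | 0.092 |

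The paired column takes no credit for any gain in precision from pairing.

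**The case against.** The strongest reply is that RQ2 and the primary outcome are descriptive, that a mixed model with time answers them, and that nowhere is an action-group or partners-group slope expressly attributed to RESPOND. That stands. A reader might infer that all regional change will be credited to the intervention; the documents support only that one clause of the aim invites this.

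Three other strong readings are tempting and also go too far.

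- **That the partners group has no unexposed survey.** The Abstract, Table 1 and Trial status together allow a 2019 wave before commencement. One such wave still gives no prior slope. A level shift after 2019 can be fitted only by extending the later straight line back a year, and that is not a change in trend.
- **That the action-group step contrast is a randomised test of intervention against none.** Both arms are exposed. Communities were randomised, but members join after allocation through workshops the intervention runs, and step 1 respondents in 2021 are those still active. Same-year comparison removes common drift but admits differential selection. Its plausible half-width (0.046 to 0.092) is also about as large as the illustrated drift of 0.08. The causal question should therefore not be moved from the network to this contrast.
- **That the step term is certainly absent from the action-group model.** The word *additionally* could mean on top of the network terms. If so, the 2021 breakpoint comes too, with no earlier step 2 action-group data to work on. Either reading needs a correction.

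The Abstract's mention of a pre-commencement measurement at all three levels does not rescue the action groups. The specific statement in Outcomes puts their first survey after GMB 3. An unseen analysis plan could settle the model terms, but it could not supply unexposed data.

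**Conclusion.** The point holds in limited form. The aim of testing whether the intervention changes trends is written for all tiers, while only the network's survey calendar can separate exposed from unexposed time. The tiers that cannot do so hold 97.8% to 98.8% of the maximum observations, depending on how the 2019 partners-group wave is classed. The tier that can has 10 members, about 6 to 7 expected per wave. Even there, unexposed means before the member's own community starts, since the network exists to share experience across communities.

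The conclusion rests on the survey calendar and on reading Local Implementation Groups as the Community Action Groups. It does not depend on the assumed drift, SD or ICC. RQ2 as posed, change during participation, remains answerable.

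**What to change.** In the RQ2 analysis paragraph:

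1. Limit the question of whether the intervention changes trends to the network model, and state beside it the 10 members and the 6 to 7 expected at 65% response.
2. Describe partners-group trends and within-step action-group trends as change during participation, not as induced by the intervention.
3. For the action groups, specify step allocation, categorical year, randomisation pair, and community and participant as random effects, with no 2021 breakpoint. Report the step 1 minus step 2 difference in 2021, 2022 and 2023 as longer versus shorter exposure, about two further years after GMB 3.
4. Report with that contrast that members joined after allocation and that step 1 respondents in 2021 are those still active.
5. Say whether the 2019 partners-group survey preceded component 1.

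The cost is a change of wording and about one extra model term, with no new data. The downside is that the added contrast is imprecise with five communities per step and remains open to selection, so it supports only a modest claim.

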### Participants

Members of each of the groups within the RESPOND governance structure (as shown in Fig. 2) will be invited to participate in the Knowledge & Engagement Survey. This includes a single overarching Regional Partners Group (RPG) which comprises senior executive representation from all partners to the National Health and Medical Research Council (NHMRC) grant. This to date includes in alphabetical order: Beechworth Health Service, Central Hume Primary Care Partnership, Gateway Health, Goulburn Valley Primary Care Partnership, Greater Shepparton City Council, Lower Hume Primary Care Partnership, Numurkah District Health, Upper Hume Primary Care Partnership, VicHealth, the Victorian Department of Education and Training, the Victorian Department of Health and Human Services and Yarrawonga Health. This group provides overarching direction and governance of the RESPOND project. The Regional Implementation Network (RIN) comprises operational and co-ordinator level staff from each of the partner agencies (listed above), along with representation from each of the implementation communities (who are not necessarily signed partners to the grant). This network provides connections and knowledge exchange between the RPG and the individual communities and provides a forum for learning and sharing of experience among the individual communities. The third group comprises the 10 community action groups (CAG), one within each community whose role is to coordinate the implementation of local intervention activities. Participants will be invited to participate in the trial at each data collection point. Any contact details obtained at baseline or at follow-up data collection points will be retained subject to our ethics approvals and used for follow-up data collection. We will send three reminders to request participants to participate in data collection.

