**Fig. 2 Fig2:**
[figure not shown]
The RESPOND Governance Structure

The number of possible participants will be used as the denominator and is based on maximum possible participation across all tiers of the governance structure and implementation teams (Table 1).

**Table 1 Tab1:** Sampling frame: groups and estimated maximum respondent numbers per community

Governance groups	Members	Number of groups	Estimated* maximum possible participants per group	Estimated* maximum possible number of responses per time point	Proposed timelines
Regional Partners Group (RPG)	Signatories to the funded grant	1	44	44	Feb/Mar 2019–2023
Regional Implementation Network (RIN)	One prevention staff member from each community (*n* = 10)	1	10	10	Feb/Mar 2019–2023
Community Action Groups (CAG)	Participants of three workshops and community-led strategies	10	100	1000	Feb/Mar 2019–2023

*Estimated maximum participant numbers based on the current number of 12 partner organisations which may increase or decrease throughout the life course of the grant

Including baseline, for the Knowledge and Engagement Survey, there are five data collection points over the 5-year period of the grant in step 1 communities, and three data collection points in step 2 communities (this survey is administered annually). It is theoretically possible that a maximum of 4270 observations could be collected.

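### The Regional Implementation Network model tests LGA-level step with only a participant random effect, so its step standard error is right only while each LGA has one fixed respondent

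*Protocol article*

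**What the plan says.** All references are to the protocol article.

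- **Randomisation (Methods).** "The unit of randomisation and intervention (clusters) is the LGA (rather than individual children or townships"). Ten LGAs are ranked by population and paired, and one of each pair is allocated to step 1.
- **RQ2 models (Data management and analysis plan).** The common base is "linear mixed models with time as fixed effect and participant as random effect (to account for the repeated measurements"). For the RIN, "the model will further include community allocation to step 1 or 2 as fixed effect", together with a 2021 breakpoint that lets the slope change in step 2 communities. A community term appears only afterwards: "For Local Implementation Groups, the model will additionally include community as a random effect to account for clustering".
- **Who is in the RIN.** Table 1 gives "One prevention staff member from each community", ten people in one group. The Participants section says that the RIN "comprises operational and co-ordinator level staff from each of the partner agencies (listed above), along with representation from each of the implementation communities", and gives no number.
- **Follow-up.** The RIN is surveyed at all five time points (Outcomes). Invitations go out at each data collection point (Participants). The identifier follows the respondent over time (Data collection). The expected RIN response rate is 65% (Recruitment).

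**The concern.** Step is a property of the LGA, so a comparison of step 1 with step 2 can rest on no more than ten independent units. A participant random effect handles repeated answers from one person. It does not handle two people who share an LGA, whether they serve together or one replaces the other. The model would treat such people as separate, independent carriers of the randomised factor. The plan accepts that LGA clustering matters, because it adds a community effect for the local groups, but it names none in the RIN model, which also tests an LGA-level factor. At stake is the precision claimed for the RIN step term: the interval would be too narrow and the type I error above its nominal level.

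**Working it through.** **1. The plan's own count.** Taking ten RIN members at five waves, with Table 1's other groups: 44×5 + 10×5 + 5×100×5 + 5×100×3 = 220 + 50 + 2,500 + 1,500 = 4,270. This reproduces the stated maximum, so the sampling frame counts one RIN respondent per LGA.

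**2. Model.** For LGA j, person i and year t = 0 to 4 (2019 to 2023), the mean is b0 + b1·t + b2·S + b3·S·max(t − 2, 0), where S = 1 for step 2.

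- True covariance: V = vL (same LGA) + vP (same person) + vE (residual).
- Covariance in the fitted model: M = (vL + vP) (same person) + vE.
- With W = M⁻¹ and A = (X′WX)⁻¹, the reported SE is √diag(A) and the true SE is √diag(A X′W V W X A). Their ratio (true to reported) is r.
- Type I error at nominal 5% is about 2[1 − Φ(1.96/r)].

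**3. Inputs.** Ten LGAs, five waves and 65% response come from the protocol. The following are assumptions, because the protocol gives no such figures: vE = 0.5 of total variance, vL = 0.15 to 0.30, vP = 0.5 − vL, yearly turnover 0 or 25%, and one to three members per LGA.

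**4. Why the number of people per LGA decides it.** With m people per LGA and no turnover, the between-person part of an LGA mean has variance (vL + vP)/m in the fitted model and vL + vP/m in truth. The gap is vL(m − 1)/m. For m = 1 it is zero. For m = 2 and vL = 0.15, the model uses 0.5/2 = 0.25 and the truth is 0.15 + 0.35/2 = 0.325. Residual variance adds to both and dilutes the ratio.

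**5. Results for the step main effect.**

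| RIN composition | SE ratio r | Type I error |
|---|---|---|
| One fixed person per LGA | 1.000 | 5% |
| One seat, 25% yearly turnover | 1.05 to 1.10 | 6 to 7.5% |
| Two to three members, no turnover | 1.09 to 1.34 | 7 to 14% |
| Two to three members, 25% turnover | 1.16 to 1.49 | 9 to 19% |

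**6. Sensitivity.** A second run used full response, equal residual and between-person variance, and an LGA share of 0.1 to 0.5 of the between-person part. It gave r = 1.000 for one fixed person, 1.03 to 1.14 for one seat replaced once at 2021, 1.04 to 1.18 for two members and 1.08 to 1.33 for three.

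**7. Slope change after 2021.** A constant LGA offset largely cancels from within-person change. With an LGA intercept only, r was about 0.96 to 1.00 in all these settings. It rose to 1.04 to 1.49 only when LGAs were also assumed to differ in slope (yearly slope variance 0.02 to 0.05).

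**The case against.** The strongest reply is that Table 1 settles the matter. It puts one prevention staff member per community in the RIN, and the 4,270 total counts it that way. The participant intercept is then the LGA intercept, r is exactly 1, and a separate LGA variance could not be estimated. On that frame it is coherent to add community only for the local groups, which have up to 100 people per LGA. This stands in full, so a reader who infers that the RIN standard errors are wrong as the plan is written goes too far.

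It does not close the point, for two reasons. The Participants section describes a larger RIN, and nothing says that the same ten people will answer for five years. A successor in the same LGA enters the model as a new independent unit.

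Other parts of the reply also stand:

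- The variance shares, turnover and members per LGA are assumptions. Under Table 1's single seat the effect is modest even with turnover.
- Agency staff are not tied to LGAs in the text, and some partners are state departments. An LGA effect alone would not place them.
- RQ2 asks whether the intervention changes trends. The slope term carries that question, and a missing LGA intercept hardly touches it. A reader might infer that the intervention result itself is overstated. The documents do not support that without an added assumption about LGA slopes.
- A reader might also infer that the RIN is the only tier with a step contrast, or that the Regional Partners Group has the same fault. The word additionally in the local-group sentence may mean that the local model carries the step terms too. The Regional Partners Group model has no randomised factor.

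**Conclusion.** The point holds conditionally. The RIN model is sound if each LGA has one unchanging respondent. It understates the standard error of the step main effect if an LGA has more than one respondent over the study, at once or in succession. The true standard error would then be about 5-10% larger than reported for one seat with 25% yearly turnover, and about 9-34% larger for two to three members per LGA without turnover. Both ranges assume an LGA share of 0.15 to 0.30 of total variance and a residual share of 0.5. The two descriptions of RIN membership do not show which case applies, and that inconsistency needs repair in any event. The change is worth making because it does no harm in the first case and corrects the second.

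**What to change.** 1. Reconcile the Participants section with Table 1 on who belongs to the RIN. State how agency staff who do not belong to a single LGA are assigned a step, or how they are handled if they cannot be.
2. In the RQ2 text, include LGA as a random intercept in the RIN model. Nest participant within LGA where an LGA has more than one respondent over the study. Where person and LGA coincide throughout, use LGA alone as the grouping unit, since the two variances cannot then be separated.
3. Base the degrees of freedom for the step terms on the ten LGAs, for example by the Kenward-Roger method.

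The cost is a short change to the text and slightly wider intervals for the step term. No new data are needed for respondents with an LGA, because LGA must already be known to assign step. With about 6 or 7 responses per wave under Table 1 (10 × 0.65 = 6.5), the nested model may prove hard to fit, which is why the fallback to LGA alone should be written down in advance.
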